Second, we will explore the feasibility and acceptability of the treatment model among depressed adolescent mothers and their families. Evidence of feasibility with this population will be demonstrated by quality of delivery (strong therapist-family working alliance) and retention of at least 80% of families. Evidence of acceptability with this population will be demonstrated by high family responsiveness through completion of homework assignments and report of high satisfaction with treatment.

Finally, we will explore preliminary impacts of the treatment on maternal depressive symptoms and parental empathy, and family emotion regulation and family functioning at 2 months post-intervention. We hypothesize that mothers will show a clinically meaningful reduction in depressive symptoms and improvements in parental empathy at 2 months post-intervention. When compared to adolescent mothers who were previously enrolled in home visiting, those who received the study treatment will show preliminary evidence of a greater reduction in depression. We also hypothesize that families will show clinically meaningful improvement in emotion regulation and family functioning.

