### Inclusion criteria for home visitors and families

Home visitors must be willing to participate in the study. Home visitors must intend to remain in their current jobs for at least 12 months. Finally, home visitors must be fluent in English since the training on study responsibilities, treatment model, implementation meetings, and supervision sessions will be carried out in this language.

Adolescent mothers, ages 13–25, in the first trimester of pregnancy through 18 months postpartum with *Edinburgh Postnatal Depression Scale* (*EPDS*) [45] scores of ≥ 8 will be recruited for study participation. At least one of the adolescent mother’s family members must be willing and available to participate in eight of the 10 video-based family therapy sessions. All families must be fluent in English and have a consistent Internet access (i.e., subscribe to an Internet service provider and do not experience weekly disruptions in service) on a cell phone or computer equipped with a camera and microphone.

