### Procedure

#### Recruitment and consent process

Willing home visitors will be recruited and consented after site presentations about the study goals, procedures, and potential benefits and risks. Home visitors will be educated on the family inclusion and exclusion criteria. Home visitors are expected to routinely screen mothers for depression and provide mental health referrals to those who screen positive for depression on the *EPDS*. Home visitors will use this standard practice to identify eligible adolescent mothers for recruitment, as it increases the generalizability of our findings. Home visitors will provide those with *EPDS* scores of ≥ 8 with two options: (i) study participation or (ii) referral for mental health services in the community. Home visitors will present a script to eligible families that include the study goals, treatment, and potential benefits and risks. The home visitor will provide each interested family’s contact information to a research assistant who will call the family to schedule a meeting to review the consent and assent forms and obtain written informed consent from all willing participants. Families will be informed that participation is voluntary and they can receive home visiting regardless of whether or not they decide to participate in the study.

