#### Study measures

Treatment implementation practices and both process and outcome measures will guide the translation of research to clinical practice. Process measures include indicators of feasibility (knowledge, adherence, quality of delivery, and retention) and acceptability (home visiting staff and family responsiveness). The process measures were selected using criteria by Mowbray, Holter, Teague, and Bybee (2003) [46]. The study measures are presented in Table 1.

**Table 1 Tab1:** Study measures by aim, construct, respondent, and time point

Construct	Measure	Respondent			Time point		
		Mother	Family	Home visitor	O_1_	O_2_	O_3_
1. Feasibility and acceptability of implementing the treatment in HV.							
Knowledge	Pass test on the use of video software.			X	X		
	Percent of eligible families identified.^a^			X		X	
Adherence	Percent of families educated in use of video software.^b^			X		X	
	Percent of visits with coping skill reinforcement.^b^			X		X	
Home visiting Staff responsiveness	Percent of training sessions attended.^a^			X	X		
	Percent of supervision sessions attended.			X		X	
	Percent of implementation meetings attended.^a^			X		X	
	Satisfaction, usefulness, and relevance of family support team responsibilities from focus groups.			X			X
2. Feasibility and acceptability of implementing treatment with families.							
Quality of delivery	Working Alliance Inventories—therapist and client versions [49, 50].^c^	X	X			X	X
Retention	Percent of families who complete treatment.	X	X				X
Family responsiveness	Percent of completed homework assignments.	X	X			X	
	Satisfaction questionnaire developed by team.	X	X				X
3. Evidence of clinical effectiveness of the treatment.							
Depression	SCID-V Depression Module [55]; NIMH DISC-Y and DISC-P Mood Module for those under 18 [56].^d^	X				X	
	Beck Depression Inventory-II (BDI-II) [57].^d^	X				X	X
Emotion regulation	Emotion Regulation Questionnaire (ERQ) [58], ERQ Child and Adolescent Version for those under 18 [59].	X	X			X	X
Parental empathy	Adult Adolescent Parenting Inventory-II (AAPI-II) [60].	X				X	X
Family functioning	Protective Factors Survey, Family Functioning/Resiliency subscale [61].	X	X			X	X

^a^Co-investigators will monitor recruitment of families and record HV staff attendance

^b^Based on home visitor report to the therapist

^c^Monitoring measure, also completed by therapist, at the end of therapy session 6

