For the third aim, the internal consistency of each outcome measure will be assessed. Basic sample statistics (e.g., means, proportions, 95% confidence intervals) will be used to characterize family baseline, post-treatment, and follow-up measures. Difference scores will be calculated, and treatment impacts on outcomes will be explored from baseline to post-treatment to follow-up. Evidence of effectiveness will be demonstrated at follow-up by significant reductions in depressive symptoms and emotional suppression, and significant improvements in cognitive reappraisal, parental empathy, and family functioning. We will compare changes in *EPDS* scores of previously enrolled adolescent mothers to those of adolescent mothers who received the study treatment at 6 months post-enrollment in the HV program. Evidence of effectiveness will be demonstrated by significantly lower *EPDS* scores in adolescent mothers who received the study treatment.

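### The only between-group comparison reads EPDS at 6 months after home-visiting enrolment, a date nothing ties to therapy, so some treated scores could precede or overlap treatment

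*Protocol article*

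**What the plan says.** Under Planned analyses, the third aim has two parts. The within-group part follows treated families from baseline to post-treatment to follow-up. The between-group part is the only one with a comparator, and EPDS is its only outcome: "We will compare changes in *EPDS* scores of previously enrolled adolescent mothers to those of adolescent mothers who received the study treatment", with the time point given as 6 months after enrolment in the home-visiting program (the sentence ends "adolescent mothers who received the study treatment at 6 months post-enrollment in the HV program"). The success rule is "Evidence of effectiveness will be demonstrated by significantly lower *EPDS* scores in adolescent mothers who received the study treatment".

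Study purpose and aims times the third aim from treatment, ending with "family emotion regulation and family functioning at 2 months post-intervention". The later sentence that predicts a greater fall in depression than in previously enrolled mothers gives no time point.

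Mothers are eligible "in the first trimester of pregnancy through 18 months postpartum" with an EPDS of 8 or more. They are found through routine EPDS screening: "Home visitors will use this standard practice to identify eligible adolescent mothers for recruitment". The Participant selection section matches historical mothers on EPDS taken at equivalent intervals, among other factors, but does not say from what date the interval runs. In Table 1, under "3. Evidence of clinical effectiveness of the treatment", depression is measured by diagnostic interview and BDI-II. EPDS is not listed.

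**The concern.** Every other third-aim analysis runs on a treatment clock. The controlled comparison runs on a program clock, and no section connects the two. A mother who had been in home visiting for more than 6 months at her first session would contribute an outcome score from before any therapy. One who had been in for 4 to 6 months would generally contribute a score from partway through. Both would be analysed as treated.

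If therapy works, such scores carry none or only part of its effect, so the contrast shrinks by an amount that depends on who happens to be recruited. A null result could then reflect timing alone, and it would be hard to interpret in the larger study that this pilot is meant to inform.

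**Working it through.** The article has no power or sample-size figure to reproduce: 12 per group was set with community stakeholders, and the study is declared unpowered. The check is calendar arithmetic.

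**Inputs**
- Comparison time: 6 months after program enrolment (Planned analyses). 6 × 52.18/12 = 26.1 weeks.
- Therapy: 10 weekly sessions (Intervention), so session 10 falls 9 weeks after session 1.
- Follow-up: 2 months after the intervention (Study purpose and aims). 2 × 52.18/12 = 8.7 weeks.
- T, the time from program enrolment to session 1: not stated.

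**Where the 6-month EPDS falls**
- Before therapy if T > 26.1 weeks.
- During therapy if T lies between 26.1 − 9 = 17.1 and 26.1 weeks.
- After the last session if T < 17.1 weeks.
- At or after the 2-month follow-up if T < 26.1 − 9 − 8.7 = 8.4 weeks.

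If sessions slip so that the last falls 10 weeks after the first, the last two limits become 16.1 and 7.4 weeks.

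**Do the documents limit T?** No. The eligibility window concerns pregnancy stage and infant age, not time in the program. Recruitment uses routine screening, not the enrolment visit. The denominator for the identification target under Planned analyses is families in the site's database who are regularly receiving visits, that is, existing clients. Neither the inclusion nor the exclusion criteria restrict time in the program.

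**How many of 12 scores could be affected?** Assume T is uniform on 0 to M months, with m = M × 52.18/12 weeks. This distribution is an assumption; nothing in the article supports a particular M.
- Share before therapy = max(0, m − 26.1)/m.
- Share after the last session = min(m, 17.1)/m.
- Share during therapy = the remainder.

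| M (months) | Before | During | After last session | Expected before or during, of 12 |
|---|---|---|---|---|
| 3 | 0% | 0% | 100% | 0 |
| 4 | 0% | 2% | 98% | 0.2 |
| 6 | 0% | 34% | 66% | 4.1 |
| 9 | 33% | 23% | 44% | 6.8 |
| 12 | 50% | 17% | 33% | 8.1 |
| 18 | 67% | 11% | 22% | 9.4 |
| 24 | 75% | 9% | 16% | 10.0 |

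For M = 12: m = 52.2, before = 26.1/52.2 = 50%, after = 17.1/52.2 = 33%, during = 17%, and 12 × 0.67 = 8.1 using unrounded shares.

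**With a treatment anchor.** The 2-month follow-up falls 9 + 8.7 = 17.7 weeks after session 1. Family baseline is up to 2 weeks before session 1, so the follow-up is about 18 to 20 weeks after baseline. Every treated reading is then post-treatment, whatever T is.

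**The case against.** The strongest reply is that the harm is unproven. If mothers start therapy soon after joining home visiting, every 6-month score is post-treatment. This stands: a reader might infer that many scores will be taken too early, but the article does not give time in the program and so supports only that they could be.

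A reader might also take the window up to 18 months postpartum as evidence of long program tenure. It is not: a mother 15 months postpartum may have joined last month.

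The matching on EPDS at equivalent intervals is a partial safeguard. It aligns the two groups with each other, but its origin is undefined and it does not place the treated score after therapy.

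The sentence may simply be loose. A change from the qualifying EPDS cannot be formed with a score that predates it, so the authors may never have meant to use such scores. It could also be parsed as treatment received at 6 months, though no other section supports this, and the comparison would then have no stated outcome time. Either way the sentence needs correcting.

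The absence of EPDS from Table 1 might suggest that no EPDS will exist after treatment. That does not follow, since home visitors screen with it routinely. It shows only that no EPDS is listed among the study measures at the time when the comparison needs one.

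Finally, this is an exploratory contrast in an unpowered pilot. The feasibility and acceptability aims are untouched, and BDI-II is measured at baseline, post-treatment and follow-up on the treatment clock. That lowers the importance of the point. It does not answer it, because timing affects validity rather than power, and the plan still attaches a rule for demonstrating effectiveness to this comparison.

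**Conclusion.** The point holds as a badly fixed time anchor. As written, the rule allows pre-therapy or mid-therapy EPDS scores to count as treated outcomes whenever session 1 comes more than about 17 weeks after program enrolment, and nothing in the article prevents this. The number affected runs from none to most of the 12, depending on unstated program tenure; the counts above rest on an assumed uniform distribution. The direction, if therapy is beneficial, is toward no effect.

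The loss in EPDS points cannot be given, because the article states neither an expected effect nor how early in therapy it appears. Nor does the article show a flat contradiction of the between-group hypothesis, since that sentence carries no time point; the mismatch is with the treatment-based timing of the aim as a whole. The wording is worth correcting because this is the only controlled comparison and the correction is cheap. It does not threaten the study's main aims.

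**What to change.** In Planned analyses, replace the 6-month program-enrolment time point with one anchored to treatment: EPDS at the 2-month follow-up, analysed as change from the qualifying EPDS.

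For each matched historical mother, take her own first qualifying EPDS as the index score. As her outcome, use the routine EPDS closest to the elapsed interval of her treated match, within a window fixed before records are extracted. State in Participant selection that the equivalent intervals run from the qualifying EPDS, so that the section agrees with Planned analyses.

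Add EPDS to Table 1 at family baseline and at the 2-month follow-up, so that the score is available for every treated mother who is followed up.

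The cost is revised wording, one extra use of a screen already given routinely, and the passing over of historical records with no EPDS in the window, which may make 12 matches harder to find.

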**Methods:**

This study protocol includes a description of an implementation-effectiveness hybrid trial design that will include 12 depressed adolescent mothers and their family members and a historical comparison group of 12 previously enrolled adolescent mothers.

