### Participant selection

The two Federal HV Program sites employ a total of 10 home visitors and serve about 44 families in three counties in New England. Eight home visitors and 12 adolescent mothers (pregnant *and* post-delivery), ages 13–25 years old, and their family members (six families per site) will be recruited. “Family member” is defined as one who is biologically related to the adolescent mother or a significant close other with whom she is not biologically related. The sample size was determined in consultation with our external community stakeholders. They recommended that we implement the protocol in two different Federal HV Program sites with a small number of families (i.e., 6 per site) in order to obtain early evidence of feasibility (e.g., implementation strategies such as staff training, research strategies such as family recruitment and retention) and acceptability (e.g., perceived agency burden, family receptivity) in preparation for larger studies of potential effectiveness and scalability.

This study also includes a historical comparison comprised of 12 depressed adolescent mothers who were previously enrolled in home visiting and have similar characteristics to those who will be recruited for the study. We will match the previously enrolled adolescent mothers to intervention group mothers based on scores of the *Edinburgh Postnatal Depression Scale* (*EPDS*) [45] administered at equivalent time intervals, maternal age, home zip code, pregnancy trimester or infant age for postpartum adolescents, relationship status, average annual income, and highest level of education.

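### The EPDS success rule is about score level, while the stated comparison and the hypothesis are about change; one quantity should be fixed

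*Protocol article*

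**What the plan says.** Three statements in the protocol article define the comparison with the historical group.

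- Hypothesis (Study purpose and aims): compared with previously enrolled mothers, "those who received the study treatment will show preliminary evidence of a greater reduction in depression". This is change.
- Comparison (Planned analyses, third aim): "We will compare changes in *EPDS* scores of previously enrolled adolescent mothers to those of adolescent mothers who received the study treatment". This is also change. The time point is six months after a mother joins home visiting.
- Success rule (the next sentence of Planned analyses): "Evidence of effectiveness will be demonstrated by significantly lower" values of the EPDS among treated mothers. This is level.

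On the design, the Abstract says the study "will include 12 depressed adolescent mothers and their family members and a historical comparison group of 12 previously enrolled adolescent mothers". Participant selection says "We will match the previously enrolled adolescent mothers to intervention group mothers based on scores of the" EPDS and on six further characteristics: age, zip code, trimester or infant age, relationship status, income and education. The Study design section states that there is no randomisation. The Discussion and Limitations say that the study is not powered for statistical differences and that its results are not meant to test impact.

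**The concern.** This is the only between-group effectiveness rule in the article, and it judges a different quantity from the one the hypothesis predicts and the preceding sentence compares. In a randomised trial, level and change share the same expected treatment effect. Here the groups are not randomised, so any baseline EPDS gap left after matching passes into one estimate and not the other. Treated mothers who started lower could end lower without having improved more, and the rule would still declare effectiveness. The reverse can also happen. With two criteria available, the choice between them also remains open after the data are seen.

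An analysis plan could not carry out all three statements as written; it would have to override one of them. That makes this a conflict in the text and not a detail left for a later document.

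**Working it through.** **Inputs from the article.** 12 mothers per group (Abstract; Participant selection); matching on seven characteristics including EPDS (Participant selection). The article gives no EPDS standard deviation, baseline/follow-up correlation, test or significance level for this comparison, so there is no figure to reproduce.

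**Assumptions, not from the article.** Normal scores with SD 1, correlation r = 0.3, 0.5 or 0.7, true difference 0.8 SD, two-sided 5% level, 8,000 simulated trials per setting. A positive verdict means p < 0.05 in favour of treatment on an unpaired t-test.

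**Step 1: how the two estimates are related.** Write X for mean baseline and Y for mean follow-up, with T for treated and H for historical.

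- Level estimate: Y_T − Y_H
- Change estimate: (Y_T − X_T) − (Y_H − X_H) = (Y_T − Y_H) − (X_T − X_H)

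They differ by exactly X_T − X_H, the baseline gap.

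**Step 2: a numerical illustration.** Suppose treated mothers go from 11 to 8 and historical mothers from 14 to 9. The level estimate is 8 − 9 = −1, which favours treatment. The change estimate is (−3) − (−5) = +2, which favours the historical group. The difference between the estimates is 3 points, equal to the baseline gap. This shows what is possible, not what is likely.

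**Step 3: how large the baseline gap may be.** Without matching, its SD is √(2/12) = 0.41 SD units. With near matching (within-pair baseline difference of SD 0.3), it is 0.3/√12 = 0.09. With exact matching it is 0.

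**Step 4: how often the two verdicts differ.**

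| Matching on baseline EPDS | SD of gap | r = 0.3 | r = 0.5 | r = 0.7 |
|---|---|---|---|---|
| None | 0.41 | 31% | 35% | 41% |
| Near | 0.09 | 18% | 15% | 27% |
| Exact | 0 | 16% | 13% | 24% |

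Under exact matching the point estimates coincide. The verdicts still differ because the standard errors do.

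**Step 5: how often the estimates have opposite signs.** At a true difference of 0.8 SD this occurs in 5.3%, 4.1% and 2.7% of trials without matching (r = 0.3, 0.5, 0.7), in 0.9%, 0.6% and 0.2% with near matching, and never with exact matching. Different significance verdicts are thus much more common than opposite directions.

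**Step 6: precision.** For two unmatched groups, variances relative to level are 1 for level, 2(1 − r) = 1.40, 1.00, 0.60 for change, and 1 − r² = 0.91, 0.75, 0.51 for the baseline-adjusted estimate. The adjusted standard error is therefore 5%, 13% and 29% smaller than for level (1 − √0.91, 1 − √0.75, 1 − √0.51), and 19%, 13% and 8% smaller than for change (1 − √(0.91/1.40), 1 − √(0.75/1.00), 1 − √(0.51/0.60)).

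Under exact matching the estimates themselves no longer differ in precision; what matters is whether the test respects the matching. Simulated power is then:

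| Analysis, exact matching | r = 0.3 | r = 0.5 | r = 0.7 |
|---|---|---|---|
| Level, unpaired | 0.46 | 0.47 | 0.46 |
| Change, unpaired | 0.33 | 0.47 | 0.69 |
| Level, paired | 0.46 | 0.55 | 0.70 |
| Baseline-adjusted | 0.50 | 0.59 | 0.74 |

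**The case against.** A reader might infer that the plan ignores baseline EPDS and the matching altogether. The article does not support that. A change score uses the earlier EPDS by construction, and EPDS is a matching variable. What is absent is a named adjusted or paired model, and a condensed article may leave that to the full plan. The absence is not a finding in itself.

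A reader might also infer that the plan gives up 5% to 29% of precision. Those figures are correct arithmetic for unmatched groups at assumed correlations, but these groups are matched on EPDS. With exact matching, the gain of the baseline-adjusted analysis over a paired comparison of levels is about 4 percentage points of power.

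Nor is the illustration in Step 2 a forecast. If the EPDS standard deviation were 4 to 5 points (an assumption), a 3-point gap would be 0.60 to 0.75 SD, far beyond what near matching would leave.

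Two further objections have some force. The stakes are limited: the aim is exploratory and the authors disclaim power and tests of impact. And baseline adjustment is a choice: in non-randomised groups, adjusted and change estimates can target different quantities, and moving the success rule to change would also end the contradiction. Neither objection removes the conflict, because the article still declares evidence of effectiveness from a rule that does not match its own hypothesis.

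**Conclusion.** The mismatch is real and should be repaired: hypothesis and comparison concern change, the success rule concerns level, and the two estimates differ by the baseline EPDS gap. That relation is exact and needs no assumption.

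How often it matters does rest on assumptions. With 12 per group and a true difference of 0.8 SD, the two verdicts differ in 13–27% of simulated trials when matching on baseline EPDS is near or exact, and in 31–41% with none. Where this study would fall is unknown: seven characteristics must be matched at once, the size of the historical pool is not stated, and the two sites currently serve about 44 families. Any precision gain depends on the correlation, which the article does not give, and on the closeness of matching, so no single figure can be claimed.

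**What to change.** In Planned analyses, replace the change sentence and the level sentence with one EPDS estimate, and align the hypothesis in Study purpose and aims to it. The preferred estimate is the between-group difference in 6-month EPDS adjusted for baseline EPDS, from an analysis that respects the matching. Say which EPDS administration serves as baseline in each group. Report the estimate with a 95% CI in place of a significance rule, since the study is not powered. Show raw change by group as description.

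The cost is analysis wording only. EPDS is already the entry screen and a matching variable, so no new data are needed. The baseline covariate takes one degree of freedom: 24 − 3 = 21 residual, against 22 for an unpaired t-test. Fitting pairs as fixed effects costs more: 24 − 12 − 1 − 1 = 10 residual. If pairs are very close on EPDS, the within-pair baseline slope would also be poorly estimated, so the way the matching is handled should be chosen with that in mind.
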